### Sample size

For the sample size calculation we used the statistical package G*power 3.0.10 [54]. We utilized the equation for sample size required per group using an unpaired t-test to compare differences between two independent means. To detect a minimal clinically important change of 0.26 points [39] in mean HAQ scores between both groups, assuming a SD of: 0.66 (SE*√N = 0.04*√271 = 0.66) [40] with 80% power and a two-sided 5% level, we will need 102 patients per arm (effect size is 0.26/0.66 = 0.39). The abovementioned sample size calculation is relevant for analyses with independent t-tests.

In our analyses, however, we will use the baseline HAQ as a covariate. By a straightforward generalisation of the method described in Borm et al [55], it can be shown that in this case the sample size must be multiplied by (1-(k-1)ρ)/k - ρ_B_^2 ^(see note below), where k is the number of follow-up assessments (3 in our case), where ρ_B _is the correlation between the outcome measured at baseline and at follow-up and where *p *is the correlation between the follow-up measurements. Although some publications report test-rest correlation for the HAQ of more than 0.8 (31), there is no direct information about the correlation that is to be expected in our trial. We expect ρ_B _to be smaller than *p *(even within the treatment groups), because the interventions will be 'between' the baseline and follow-up assessments. The interventions may not have the same effect on all patients and therefore decrease the correlation. When *p *is between 0.7 and 0.9 and ρ_B _= p-0.2, the sample size can be reduced by a (design) factor 0.44 to 0.55. For p between 0.8 and 0.9 and ρ_B _= *p*-0.1, the sample size can be reduced by a factor 0.38 to 0.44. A trial with 55 patients per treatment group will then have at least 80% power (when the design factor is 0.55). In the most optimistic scenario, when the design factor is 0.38, the study has slightly over 90% power.

Finally, as the patients will be treated in groups (cluster) of approximately eight, the patient numbers have to be increased by a factor 1+(8 -1)*ICC. For ICC = 0.05, this leads to 74 patients. In order to compensate for possible drop-outs (15%), we plan to enrol 85 patients per treatment group.

Note:

When Y = mean(Y_1_, ...Y_k_) and the baseline and follow-up measurements Y_i _all have standard deviation σ, the variance of Y is ((1+(k-1)*p*)/k)σ^2^, the correlation between B and Y is k ρ_B_/sqrt(k+(k(k-1) p) and the formula in Borm *et al *yields the design factor (1-(k-1)*ρ*)/k - ρ_B_^2^.

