#### Clinical efficacy

The primary variable, HAQ during the first year after treatment, will be analysed with a random effects model with the HAQ scores after 6, 26 and 52 weeks as dependent variable. The fixed factors will be assessment (6, 26 or 52 weeks), treatment group, sex and baseline value. In order to account for the group wise treatment and the repeated measurements, the random effects group and patient will be included.

HAQ immediately after treatment will be evaluated in a random effects model with fixed factors treatment group, sex and baseline value, and random factor group. All other continuous variables will be analysed in a similar way. Skewed variables will be transformed before analysis. For dichotomous outcomes, random effects general linear models with Bernoulli distribution and linear link function will be used, similar to the ones described for continuous outcomes.

Changes in effect size over time will be evaluated by adding the interaction of assessment and treatment group to the model.

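### At its own planning value (design factor 0.55) the sample-size chain falls slightly short: 85 per arm gives about 78–80% power, not at least 80%, because two steps were rounded down and drop-out was added as ×1.15 instead of /0.85

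*Protocol article*

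**What the plan says.** All figures come from the protocol article, Sample size, unless noted.

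- Target: "To detect a minimal clinically important change of 0.26 points", "with 80% power and a two-sided 5% level".
- Spread: "assuming a SD of: 0.66 (SE*√N = 0.04*√271 = 0.66").
- Plain two-group t-test: "we will need 102 patients per arm (effect size is 0.26/0.66 = 0.39").
- After allowing for the baseline covariate and the average of three follow-up visits: "A trial with 55 patients per treatment group will then have at least 80% power (when the design factor is 0.55"). The design factors named run from 0.38 to 0.55. The 80% statement is tied to 0.55, the least favourable of them.
- After multiplying by 1 + (8 − 1) × ICC for treatment in groups of about eight: "For ICC = 0.05, this leads to 74 patients".
- After drop-out: "In order to compensate for possible drop-outs (15%), we plan to enrol 85 patients per treatment group". The Abstract gives the total as 170.

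Under Planned data analysis, Clinical efficacy, the primary model accounts for groups and repeated visits: "the random effects group and patient will be included". The article does not say which degrees of freedom the treatment test will use.

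**The concern.** The article attaches a guarantee of at least 80% power to a specific planning value and then carries that number through clustering and drop-out to 85 per arm. If the steps are not carried out correctly, the guarantee fails at the value to which it is attached. The correlations behind 0.55 are, by the article's own account, not directly known, so 0.55 is the value a cautious reader will use.

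This is a superiority comparison between two similar programmes, and the Discussion itself names limited contrast as a possible limitation. A null result is therefore plausible, and it would be judged against the stated power. The question is how large the overstatement is.

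**Working it through.** **Inputs (Sample size section).** Difference 0.26, SD 0.66, two-sided 5%, 80% power, design factor f = 0.55, group size 8, ICC 0.05, drop-out 15%.

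**Reproducing the plan's chain**

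1. Plain t-test: 2 × (0.66 × (1.96 + 0.84)/0.26)² = 101.2 with unrounded normal quantiles, so 102. By noncentral t, 102 gives 79.95% and 103 is the first number at or above 80%. The 102 is acceptable.
2. Design factor: (1 + (k − 1)ρ)/k − ρ_B² with k = 3, ρ = 0.7, ρ_B = 0.5 gives 2.4/3 − 0.25 = 0.55. This uses the plus sign of the variance expression in the note; the printed factor carries a minus sign, which is a separate matter.
3. 102 × 0.55 = 56.1. The article has 55.
4. 55 × 1.35 = 74.25. The article has 74.
5. 74 × 1.15 = 85.1. The article has 85. This shows how drop-out was applied.

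**Checking each step**

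*Step 3.* Power for n independent patients per arm with variance 0.66² × 0.55:

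| n per arm | noncentral t | normal approximation |
|---|---|---|
| 55 | 78.8% | 79.5% |
| 56 | 79.6% | 80.3% |
| 57 | 80.3% | 80.9% |

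So 55 misses 80% on either basis, and 57 are needed by the t-test the article names.

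*Step 4.* 57 × 1.35 = 76.95, so 77.

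*Step 5.* To keep n after losing 15%, divide by 0.85. From the plan's own 74: 74/0.85 = 87.1, so 88. In reverse, 85 × 0.85 = 72.25, below 74.

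*Whole chain at design effect 1.35.* 102 × 0.55 × 1.35/0.85 = 89.1, so 90; rounding up at each step gives 57, 77, 91. The planned 85 is about 6% below that.

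**Power actually delivered**

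Analysed per arm: 72.25. Variance: 0.66² × f × design effect. Two design effects are plausible: 1 + 7 × 0.05 = 1.35 if eight per group are analysed, and 1 + (6.8 − 1) × 0.05 = 1.29 if groups of eight lose 15% (8 × 0.85 = 6.8).

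| f | design effect | t, 2n − 2 df | normal |
|---|---|---|---|
| 0.55 | 1.35 | 77.9% | 78.5% |
| 0.55 | 1.29 | 79.7% | 80.3% |
| 0.44 | 1.35 | 86.2% | 86.7% |
| 0.38 | 1.35 | 90.7% | 91.1% |

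**Sensitivity, resting on an assumption the article does not state.** 170/8 = 21.25, so about 21 treatment groups. If the treatment effect were tested on groups minus two, about 19 df, power at f = 0.55 would be 74.1% (design effect 1.35) or 76.0% (1.29). At f = 0.44 and 0.38 with design effect 1.35 it would be 83.0% and 88.0%.

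**The case against.** The strongest defence is that the slips nearly cancel against a conservative choice. The factor 1.35 assumes eight analysed per group. If drop-out happens within groups, 1.29 applies and the requirement is 102 × 0.55 × 1.29/0.85 = 85.1, essentially the planned 85. This stands, and it is why the shortfall is given as 0 to about 2 points. It does not rescue the derivation as printed, which uses 1.35, nor the statement about 55, which precedes any clustering.

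Other features also favour the plan. Patients who leave late still contribute earlier visits to the repeated-measures model, so treating 15% as total loss is pessimistic. The control arm has only two group sessions, yet 1.35 is applied to both arms. Both points are fair, and neither is quantified in the article.

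Three stronger readings are tempting but not supported:

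- A reader might infer that true power is about 74% because the test has only about 21 groups. The Clinical efficacy section fixes no degrees of freedom, and that choice is commonly left to an analysis plan, which is not shown here. The figure is a sensitivity value, not a misprint.
- A reader might infer a still lower power by taking the ICC of 0.05 to be on the raw HAQ scale. The article applies it to the already reduced patient number, so the natural reading is an ICC for the analysed outcome. Nothing places it on the raw scale.
- A reader might infer that 170 is too few across the board. At factors 0.44 and 0.38 power exceeds 80%, even with 19 df.

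**Conclusion.** The point holds as a small, definite error in the stated derivation. At design factor 0.55, 55 per arm gives 78.8% by the named test, and 85 enrolled with 15% lost leave fewer patients than the plan says it needs. The resulting power is about 78% (design effect 1.35) to just under 80% (1.29) with patient-level degrees of freedom; the normal approximation reaches 80.3% in the better case. The overstatement is therefore between nothing and about 2 percentage points, and it arises only at the least favourable factor.

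This rests on the article's own difference, SD, ICC and drop-out rate, on loss meaning no follow-up data, and on the ICC referring to the analysed outcome. It does not call the design or the total of 170 into question.

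**What to change.** Keep 170 and correct the Sample size section:

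- 55 becomes 57, and 74 becomes 77.
- Apply drop-out as division by 0.85, so that the chain at design effect 1.35 reads 102, 57, 77, 91 per arm.
- State what is actually enrolled and what it delivers, for example: with 85 enrolled per arm and 15% lost, power is about 78–80% at design factor 0.55, depending on whether drop-out reduces the observed group size, and about 86% and 91% at factors 0.44 and 0.38 (design effect 1.35).
- Optionally, add a sensitivity value labelled as an assumption: testing against about 21 treatment groups (about 19 df) would give about 74–76% at factor 0.55.

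The cost is a few corrected numbers and a slightly less favourable power statement. No patients are added, and the endpoint and analysis model do not change.

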### Planned data analysis

Study data are entered in Access 2003, exported to the statistical package STATA v10 stored on a secure network drive. Five percent of the data will be entered twice to assess percentage and nature of typing errors. All paper records are stored in a locked cabinet in an anonymised format. The researcher will check for any missing data and will manage this according to the recommendations of the questionnaires. Descriptive statistics will be used to determine participant characteristics. Continuous variables will be reported using means, standard deviations (SD) and inter-quartile ranges when appropriate, if not median and ranges are shown. For dichotomous/categorical variables, we will display absolute numbers and percentages. The primary analysis will be according to the intention to treat principle.

#### Clinical efficacy

The primary variable, HAQ during the first year after treatment, will be analysed with a random effects model with the HAQ scores after 6, 26 and 52 weeks as dependent variable. The fixed factors will be assessment (6, 26 or 52 weeks), treatment group, sex and baseline value. In order to account for the group wise treatment and the repeated measurements, the random effects group and patient will be included.

HAQ immediately after treatment will be evaluated in a random effects model with fixed factors treatment group, sex and baseline value, and random factor group. All other continuous variables will be analysed in a similar way. Skewed variables will be transformed before analysis. For dichotomous outcomes, random effects general linear models with Bernoulli distribution and linear link function will be used, similar to the ones described for continuous outcomes.

Changes in effect size over time will be evaluated by adding the interaction of assessment and treatment group to the model.

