### Study endpoints

Participants will receive postal questionnaires at baseline, and at 6, 13, 26, 39 and 52 weeks after the start of the intervention. The primary endpoint to study the long term effects of the interventions is the averaged HAQ-score [34] as obtained from the 6, 26 and 52 week time points. The 6 week time point will provide a secondary endpoint for investigating the short term effects of the interventions. On time points 6, 13, 26, 39 and 52 costs will be assessed.

Socio-demographic information will be collected at baseline including age, gender, employment nature and body mass index. In Table 1 we outlined all outcome measures that will be collected at baseline and at follow-up evaluations.

**Table 1 T1:** Outcome measures used at baseline and follow-up assessments

Outcome (Instrument)	Time Points (weeks)					
	**0**	**6**	**13**	**26**	**39**	**52**

						

Daily functioning (HAQ) [34]	X	X	X	X	X	X

HRQoL (RAND-36) [42]	X	X		X		X

HRQoL (EuroQol EQ-5d) [45]	X	X	X	X	X	X

Patient specific complaints (PSK) [43]	X	X		X		X

Fatigue (CIS-8) [44]	X	X		X		X

Physical activity (SQUASH) [48]	X	X		X		X

Illness Cognitions (ICQ) [65]	X	X		X		X

Patient Global Assessment (PGA) [50]		X		X		X

Self-efficacy (GSES) [51]	X	X		X		X

Kinesiophobia (TSK) [66]	X	X		X		X

Costs		X	X	X	X	X

Abbreviations: HRQoL = Health related quality of life.

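### The primary model's single treatment coefficient matches the stated endpoint (equal average of weeks 6, 26 and 52) only with complete follow-up or a constant effect; with losses after week 6 it under-weights week 52

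*Protocol article*

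**What the plan says.** Under Study endpoints, the primary endpoint is "the averaged HAQ-score [34] as obtained from the 6, 26 and 52 week time points". The note at the end of Sample size shows that a simple mean is meant: "When Y = mean(Y_1_, ...Y_k_) and the baseline and follow-up measurements Y_i _all have standard deviation σ". The trial is sized on that quantity with three follow-up assessments.

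Under Planned data analysis, Clinical efficacy, the primary model takes the three HAQ scores as the dependent variable. "The fixed factors will be assessment (6, 26 or 52 weeks), treatment group, sex and baseline value", and "the random effects group and patient will be included". This gives one treatment coefficient common to all three visits. The interaction appears as a further step: "Changes in effect size over time will be evaluated by adding the interaction of assessment and treatment group to the model". The article does not say that the primary result is an equally weighted contrast.

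On losses, Sample size says only this: "In order to compensate for possible drop-outs (15%), we plan to enrol 85 patients per treatment group". It does not say when patients are expected to leave.

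**The concern.** With complete data, the treatment coefficient of this model equals the difference in simple means, so model and endpoint agree. With incomplete follow-up, the model weights each visit by the information observed there. A patient who leaves after week 6 still informs the common coefficient, but only through week 6. If the true effect is the same at every visit, this is harmless and efficient. If it is not, the coefficient answers a slightly different question from the endpoint, and the realised drop-out decides which one.

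The article does not assume a constant effect. It sets the short-term effect at week 6 apart from the first-year effect and plans to examine change over time. Week 6 is also the end of the six-week programme, so it is a natural point for the effect to start fading, or to start growing if new habits take hold. At stake is whether the headline figure is the one-year average that the endpoint promises.

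**Working it through.** **Inputs from Sample size.** Difference 0.26; SD 0.66; k = 3; correlation ρ between follow-ups 0.7 to 0.9, with baseline correlation ρ_B = ρ − 0.2; cluster factor 1 + 7 × 0.05 = 1.35; 85 per arm; 15% drop-out.

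**Assumed, because the article gives neither.** The timing of losses (equal in both arms, completely random) and the effect profile over visits.

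**The plan's own figures.** The variance of the mean in the note leads to the design factor (1 + 2ρ)/3 − ρ_B². At ρ = 0.7 this is 0.80 − 0.25 = 0.55, and at ρ = 0.9 it is 0.933 − 0.49 = 0.44, as stated. Then 102 × 0.55 = 56.1 (stated as 55), 55 × 1.35 = 74.25, and 74 × 1.15 = 85.1. The chain to 85 reproduces, apart from 55 against 56.

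**Weights.** Given baseline, the correlation between follow-ups is r = (ρ − ρ_B²)/(1 − ρ_B²), which is 0.60, 0.69 and 0.80 for ρ = 0.7, 0.8 and 0.9. In a random-intercept model with visit effects and one treatment effect, a patient with m observed visits adds 1/(1 + (m − 1)r) to the weight of each visit observed. The weights are then scaled to sum to one.

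Take ρ = 0.8, ρ_B = 0.6, so r = 0.44/0.64 = 0.6875. Suppose 7.5% are lost between weeks 6 and 26 and a further 7.5% between weeks 26 and 52. The contributions are 1/2.375 = 0.4211 (three visits), 1/1.6875 = 0.5926 (two) and 1 (one).

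- Week 6: 0.85 × 0.4211 + 0.075 × 0.5926 + 0.075 × 1 = 0.4773
- Week 26: 0.85 × 0.4211 + 0.075 × 0.5926 = 0.4023
- Week 52: 0.85 × 0.4211 = 0.3579
- Sum 1.2376, so the weights are 0.386 / 0.325 / 0.289

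**Effect on the estimate.** The expected coefficient is the weighted sum of the visit-specific effects. Both profiles below have a true mean of 0.26 (ρ = 0.8, 15% loss):

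| Timing of loss | Weights (6 / 26 / 52) | Fading 0.40/0.26/0.12 | Growing 0.12/0.26/0.40 |
|---|---|---|---|
| No loss | 0.333 / 0.333 / 0.333 | 0.260 | 0.260 |
| Even after week 6 | 0.386 / 0.325 / 0.289 | 0.2735 | 0.2465 |
| All between weeks 6 and 26 | 0.415 / 0.293 / 0.293 | 0.277 | 0.243 |
| All after week 26 | 0.357 / 0.357 / 0.286 | 0.270 | 0.250 |
| Half before week 6, rest even | 0.361 / 0.329 / 0.310 | 0.267 | 0.253 |
| All before week 6 | 0.333 / 0.333 / 0.333 | 0.260 | 0.260 |

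Over ρ = 0.7 to 0.9 with even loss, the weights are 0.383–0.390 / 0.324–0.326 / 0.287–0.291, and the fading profile is estimated as 0.273 to 0.274. A steep fade of 0.52/0.20/0.06 (mean also 0.26) gives 0.282 to 0.284. A mild fade of 0.30/0.26/0.22 has a bias of 0.04 × (0.386 − 0.289) = 0.004. A random group effect at ICC 0.05 hardly changes the week-6 weight: 0.385 with even loss and 0.411 with early loss.

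**Against the trial's precision.** With complete data the standard error is √(2 × 0.66² × factor × 1.35 / 85), that is 0.087 for a factor of 0.55 and 0.078 for 0.44. With 15% even loss these become about 0.088 and 0.079. The bias for 0.40/0.26/0.12 is then 0.0128/0.088 = 0.15 to 0.0144/0.079 = 0.18 standard errors.

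**After the fix.** With the interaction in the model and a (1/3, 1/3, 1/3) contrast, the weights are exactly one third whatever the pattern of loss. At 15% loss, the ratio of its standard error to that of the common coefficient is 1.0005 to 1.0026 across ρ and the three timings after week 6.

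**The case against.** Four objections deserve an answer.

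First, the shift needs two conditions that the article does not state: losses after week 6, and an effect that varies between visits. That stands. The 15% comes without timing, and if half of it falls before week 6 the fading example is off by only about 0.007.

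Second, the article already plans the interaction analysis and a separate week-6 analysis, so a marked fade would probably be noticed. That also stands, and it limits the harm. It does not change the estimate reported as primary.

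Third, the exact contrast could be left to an analysis plan that is not shown. This carries less weight, because the article itself defines the endpoint and sets out the model, and the two coincide only under conditions it does not assume.

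Fourth, a reader might infer more than the documents support:

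- *That drop-out pushes the result over the 0.26 relevance threshold.* An effect of 0.48/0.24/0 (mean 0.24) would indeed be estimated as 0.257 to 0.269 at ρ = 0.8, depending on timing. But 0.26 is a relevance benchmark and the planning difference, "To detect a minimal clinically important change of 0.26 points [39] in mean HAQ scores between both groups". No decision rule is tied to the point estimate exceeding it.
- *That the benefit is always exaggerated.* The article predicts no time course, and a growing benefit would be understated.
- *That false positives arise.* If the effect is nil at every visit, the reweighting creates none.

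**Conclusion.** The mismatch between endpoint and primary model is real and follows from the article's own text. It operates only if patients are lost after week 6 and the effect differs between visits. Weight then leaves week 52. It goes mainly to week 6, or equally to weeks 6 and 26 if all losses come after week 26. Random, balanced drop-out does not prevent this.

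At the planned 15% loss the consequence is modest: about 0.01 to 0.02 HAQ points in the even-loss examples, or roughly 0.15 to 0.3 standard errors, upward for a fade and downward for a growing effect. These figures rest on the article's SD and correlations and on assumed timing and profiles. This does not threaten the trial's validity. It is worth correcting because the endpoint is stated clearly and the model can be made to match it at almost no cost.

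**What to change.** Include treatment-by-assessment in the primary random-effects model, keeping sex, baseline and the random group and patient effects as planned. Name as the primary result the (1/3, 1/3, 1/3) contrast of the three visit-specific treatment differences, with its confidence interval and test. State the contrast explicitly, because once the interaction is in the model the treatment coefficient on its own may refer to a single reference visit. The visit-specific differences and the interaction test come from the same fit and cover the planned look at change over time.

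The cost is one model term and one contrast statement. At 15% loss the standard error rises by about 0.05% to 0.3%, which needs no change to the sample size.

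### The test for change in treatment effect over time holds its 5% level only if each therapy group's effect stays constant from week 6 to week 52

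*Protocol article*

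**What the plan says.** All of the following is in the protocol article. Under Clinical efficacy, the HAQ at weeks 6, 26 and 52 is the dependent variable: "The fixed factors will be assessment (6, 26 or 52 weeks), treatment group, sex and baseline value". Treatment group here means the arm. The random part follows: "In order to account for the group wise treatment and the repeated measurements, the random effects group and patient will be included". Group here means the set of patients treated together. The question of a changing effect is then handled in one sentence: "Changes in effect size over time will be evaluated by adding the interaction of assessment and treatment group to the model". No group-by-assessment term, random slope or cluster-robust variance is mentioned.

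Under Sample size, the plan treats clustering by therapy group as important: "as the patients will be treated in groups (cluster) of approximately eight, the patient numbers have to be increased by a factor 1+(8 -1)*ICC", with an ICC of 0.05. The intervention descriptions put eight patients in a group in both arms. Week 6 also has its own separate model, with a random group factor.

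**The concern.** The null hypothesis of interest is that the arm difference is the same at all three visits. The model as written tests a narrower null: that the arm difference is constant and also that no therapy group follows its own course over time. The second condition is not part of the question.

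It may well fail. Patients in a group share a six-week programme and are then followed by postal questionnaire to week 52, so a group effect could be strongest at week 6 and change afterwards. The document gives no reason to expect it to stay fixed.

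At stake is the only stated test of whether benefit fades or grows after treatment. A false positive could be reported as a waning or emerging effect when the arm difference is constant. The clustering allowance made in the sample size and in the averaged effect does not reach this test.

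**Working it through.** **The plan's own figures.** The article states no error rate for the interaction test. Its inputs can be reproduced from Sample size:
- Unadjusted n per arm: 2 × (1.960 + 0.842)² × (0.66/0.26)² ≈ 101.2, so 102, as stated.
- Design factor (1+2ρ)/3 − ρ_B² at ρ = 0.7, ρ_B = 0.5: 0.80 − 0.25 = 0.55, as stated. This uses the plus sign of the variance expression in the note; the minus sign printed in the factor gives a negative value.
- 102 × 0.55 = 56.1 (stated 55). 55 × (1 + 7 × 0.05) = 74.25 (stated 74). 74 × 1.15 = 85.1 (stated 85).

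The ICC is applied after the design factor, so it belongs to the baseline-adjusted mean of the three visits.

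**Why the intercepts do not help.** Write the random part as g_j + p_ij + e_ijt for therapy group j, patient i and visit t. In any difference between two visits, g_j and p_ij drop out. If the group effect is really g_jt, the difference g_j2 − g_j1 remains and is shared by all patients in the group, but the model treats it as independent patient error.

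**Inputs.** ICC 0.05; ρ = 0.7, 0.8, 0.9 with ρ_B = ρ − 0.2 (plan). About 10 groups of m = 7 analysed per arm, from 85 enrolled, groups of about eight and 15% drop-out. Between-visit correlation r of group effects: **assumed; not in the document**.

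**Formulas** (balanced data, total variance 1 per visit):
- Group variance per visit, with the ICC on the adjusted averaged scale: σ_g² × (1+2r)/3 = 0.05 × DF, so σ_g² = 0.15 × DF/(1+2r).
- ICC of change = σ_g²(1−r)/(1−ρ).
- Inflation D = 1 + (m−1) × ICC of change.
- False-positive rate of the 2-df test ≈ exp(−2.996/D).

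Example, ρ = 0.9, r = 0.8: DF = 0.933 − 0.49 = 0.443; σ_g² = 0.15 × 0.443/2.6 = 0.0256; ICC of change = 0.0256 × 0.2/0.1 = 0.051; D = 1 + 6 × 0.051 = 1.31; rate = 10.1%.

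| r | ρ = 0.7 (DF 0.55) | ρ = 0.8 (DF 0.507) | ρ = 0.9 (DF 0.443) |
|---|---|---|---|
| 1.0 | 5.0% | 5.0% | 5.0% |
| 0.9 | 5.9% | 6.3% | 7.3% |
| 0.8 | 7.0% | 7.8% | 10.1% |
| 0.6 | 10.0% | 12.0% | 17.6% |

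Simulation of the same design gives 6-7%, 7-10% and 9-17% for r = 0.9, 0.8 and 0.6, within about a point of the formula.

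**Other scaling.** If the ICC of 0.05 is placed on the unadjusted per-visit variance (σ_g² = 0.05), the formula gives 6.6%, 7.4% and 10.0% at r = 0.9; 8.2%, 10.0% and 15.4% at r = 0.8; and 11.8%, 15.4% and 25.6% at r = 0.6. Simulation gives up to 10%, 16% and 26%.

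**Checks.** With the interaction tested against group-by-assessment variation, the simulated rate is about 5% in every setting. With serially decaying patient correlations and no group-by-time variance, the planned test gave 5.5-6.1%. The larger rates therefore come mainly from the omitted term and not from the equal-correlation assumption.

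**The case against.** The best defence has three parts.

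First, the article never says intercept only, and a fuller analysis plan could specify more. This has some force, since intercepts are an inference. But "the random effects group and patient will be included" lists the random effects, and the next step adds only the fixed interaction. An analyst following the text would fit two intercepts. This is a stated model, not an omitted detail.

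Second, everything turns on r, which the document does not give. Some sources of group differences, such as the two centres or the provider teams, could persist and keep r near 1. This stands: at r = 1 there is no inflation, and at 0.9 it is slight.

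Third, the analysis is secondary. Change of effect over time is not among the stated aims, and the article attaches no significance level or decision rule to it. This also stands, and it limits the consequence.

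A reader might go further and infer that standard errors for arm differences at single visits are also too small. The documents do not support making that a point. No such contrasts are planned from this model, and the one visit-specific analysis named, week 6, has its own random group factor.

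**Conclusion.** The point holds in conditional form. As written, the interaction test keeps its 5% level only when therapy-group effects are constant over weeks 6, 26 and 52. Otherwise it rejects too often: about 6-7%, 7-10% and 9-17% at group correlations of 0.9, 0.8 and 0.6, with the ICC on the scale where the plan applies it. The less favourable scaling reaches 10%, 16% and 26%.

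It is tempting to say simply that the error rate doubles. The documents do not support that as a general statement. Doubling needs D of about 1.30, which on the plan's scale means r near 0.6 at ρ = 0.7 or near 0.8 at ρ = 0.9, and no value of r is given.

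Nor does the defect reach the primary result. The averaged effect is a between-group comparison that the group intercept covers, and the week-6 model is clustered in its own right. What is affected is this secondary test, and its counterpart for any other outcome analysed with the same repeated-measures model. The remaining assumptions are the intercept reading, roughly balanced groups and an ICC of 0.05.

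**What to change.** Under Clinical efficacy, state that when the assessment-by-arm interaction is added, a random group-by-assessment effect is added with it, and that the interaction is tested with group-level degrees of freedom. With 10 groups per arm and balanced data, that is (20 − 2) × 2 = 36 denominator degrees of freedom, against (140 − 2) × 2 = 276 at patient level. An acceptable alternative is standard errors clustered on therapy group with a small-sample correction. Leave the primary averaged analysis and the week-6 model as planned.

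The cost is one sentence and one variance component, with no new data or patients. The interaction test loses some power, and the component may be estimated at zero.
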